## 6.2 Preparation/Handling/Storage/Accountability

### 6.2.1 Acquisition and accountability

This study is a behavioral interventional trial which does not include any medication. Please see section 6.1 for a detailed review of the intervention.

### 6.2.2 Appearance, Packaging, and Labeling

This study does not include any devices with packaging or labeling.

## 6.3 Measures to Minimize Bias: Randomization and Blinding

This study is a behavioral intervention study to assess the feasibility of recruitment, retention, and completion of the intervention in this population. Therefore, there is no control group and no randomization. As there is no control group, no blinding will be completed.

## 6.4 Study Intervention Compliance

Compliance will be assessed based on the completion of the INTACT intervention, as discussed in Objective 3. This consists of: meeting with a trained interventionist/coach who can provide tailored feedback and advice to the participant focused on the specific aspect of contingent caregiving covered by that month’s online module.

# 7 Study Intervention Discontinuation and Participant Discontinuation/Withdrawal

## 7.1 Discontinuation of Study Intervention

The study intervention will only be discontinued if the participant chooses to withdraw from the study (see below) or if the birthing parent participant does not retain custody of the child throughout the study. If a birthing parent participant loses their device that they use to access study activities for a period of ≥3 consecutive coaching sessions, the study intervention will be discontinued.

## 7.2 Participant Discontinuation/Withdrawal from the Study

If the birthing parent participant does not retain custody of the child throughout the study, they will also be withdrawn from the study.

A birthing parent/infant dyad may withdraw from the trial at their own request, or the site investigator can withdraw a birthing parent/infant dyad. Reasons for withdrawal may include but are not limited to:

- Birthing parent/infant choose to withdraw at their own request
- Birthing parent/infant dyad is lost to follow-up
- Birthing parent/infant dyad is unwilling or becomes unable to comply with the study procedures required by the protocol
- Birthing parent loses custody of the infant

ISPCTN site personnel will record the reasons for withdrawal in the trial documentation. Sites can replace the birthing parent/infant dyad in the case of a screen failure, including those that are deemed not eligible after obtaining informed consent and completing the cannabinoid use survey. Sites can also replace the birthing parent/infant dyad if they withdraw from the study before beginning the first month’s coaching session.

## 7.3 Lost to Follow-Up

A participant is considered lost to follow-up when there has been no contact for three consecutive coaching sessions despite maximum attempts. The site research team must make reasonable attempts to contact the participant using resources such as phone, text, email, private messaging through social media, and medical records, as permitted by the central IRB. If the coordinator is able to reach a self-identifying voicemail or responder, a reasonable attempt at contact may be defined as two texts or phone calls during working hours, one in the evening and one on the weekend. Research coordinators will keep a log of all methods utilized. Once a participant is lost to follow-up, the site research team may stop contacting them.

Participants will be asked if they are willing to provide names and contact information of back-up contact(s) or other ways for the research team to stay in contact throughout the year-long study. Participants will be informed that once the participant provides back-up/other contact information, the research team may use those method(s) to contact the participant, and that back-up contacts may then learn that the participant is part of this study.

# 8 Study Assessments and Procedures

## 8.1 Efficacy Assessments

**PRIMARY OUTCOME MEASURES**

**Objective 1 – Participant Recruitment.** All birthing parents approached by the study team for study participation will be tracked to determine the number that are approached, consented, and confirmed to be eligible for study participation. We aim to consent and confirm eligibility in at least 2-3 individuals at each site per month, with enrollment duration lasting 3 months, averaging at least 6.67 individuals per month over all sites. We will have a log of participants consented, site location, and the date. This will allow the number of individuals consented per month to be calculated. For a future randomized controlled trial, we would need to consent and maintain eligibility in at least 360 participants in total, or 20 per site in each of the 18 ISPCTN sites. This sample size will provide statistical power of 0.83 to detect a mean difference of 5 scale points between the intervention and comparison conditions on the Bayley Scales of Infant and Toddler Development, Fourth Edition, which would be the primary outcome measure. A difference of 5 scale points on the Bayley-IV is one-third of a standard deviation which equates to an effect size *d* = 0.33, which is between the thresholds for a small and moderate effect (0.20 and 0.50, respectively). The sample size estimation assumes an intra-class correlation of 0.05 within ISPCTN sites. Thus, consenting and confirming eligibility of at least 2-3 individuals per site per month in the feasibility trial will ensure that consenting and confirming eligibility in 2 individuals per site per month in a randomized controlled trial is feasible.

The proportion of birthing parent participants recruited is calculated as the number of birthing parents that are approached, consented, and determined to meet study eligibility divided by the number of birthing parents approached for participation. The number of individuals approached by a study team member will be recorded to know the proportion that consent after being approached. An approached birthing parent is defined as having a study team member discussing the trial with a possible unique participant (if the study team member discusses the trial with the same possible participant more than once, this will be documented as only 1 individual approached) with bi-directional communication. We will calculate the consented proportion to total individuals approached to inform the number of individuals that would need to be approached for a larger clinical trial. We aim to have at least 20% of approached individuals consent and be determined to be eligible for study participation.

**Objective 2 – Participant Completion.** We will calculate participant completion as the percent of birthing parent /infant dyads that complete the final monthly coaching session when the child reaches 12 months of age. The numerator will be the number of participants that complete the final monthly coaching session when the child is 12 months of age, and the denominator will be the total number of participants that were approached, consented, and determined to be eligible. We will then calculate the completion rate for each site and across all sites, with at least 70% of dyads completing the final coaching session across all sites as the goal.

**Objective 3 – Participant Adherence.** We will calculate the number of participants who receive at least 70% of the number of INTACT intervention coaching sessions. This will be done by taking the number of INTACT intervention coaching sessions completed by the study participants that were approached, consented, and met eligibility for participation. The total number of monthly coaching sessions possible will serve as the denominator (12 per dyad), and the total number of monthly coaching sessions completed by the birthing parent/infant dyad will serve as the numerator. We will calculate this ratio for each birthing parent/infant dyad and aim to have 80% of the participants complete a sufficient number of INTACT intervention coaching sessions completed, defined as at least 8 coaching sessions (70% of the total number of INTACT intervention coaching sessions possible).

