Birthing parents with a positive urine toxicology screen for THC or self-reported cannabinoid use during pregnancy will be recruited for participation. Individuals can be referred by healthcare providers, self-refer during 3^rd^ trimester obstetrical appointments after viewing flyers placed in the obstetrical and family medicine clinics, or be recruited by study staff during the birth hospitalization. Providers may give flyers individually to birthing parents in the obstetrical and family medicine clinics if the patient uses cannabinoids during the 2^nd^ and 3^rd^ trimesters in pregnancy. Individuals with a positive toxicology report for THC during the birth hospitalization will be identified by an automated daily chart review of the electronic medical records with results sent to the local study team; this automated report will ensure that the study team is aware of admissions as a prescreen for potentially eligible individuals. A partial HIPAA waiver will be obtained for pre-screening procedures used to identify potential participants. Birthing parents with a positive toxicology screen for THC or who self-report use of cannabinoids will be considered for participation in the study. Research coordinators will contact potential participants to briefly describe the study and perform a preliminary eligibility screen using the Initial Contact Script. All birthing parent use of cannabinoids will be confirmed with the Cannabinoid Use Survey only after the individual consents to study participation. Participants may feel more comfortable providing this information after the study has been described in detail, with the added assurance of confidentiality from the CoC and the HIPAA authorization. Responses to the survey will be retained in the electronic data capture (EDC) system, linked to the participant ID code.

Consent will not be obtained until after the birth of the infant to ensure that inclusion / exclusion criteria are met, and thus the cannabinoid use survey will not be completed until after the birth of the infant. For individuals that indicated interest in the study prenatally, their due date will be noted so that study staff can monitor the hospital patient census for their delivery.

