The birthing parent/infant dyads (goal n=20) will be recruited either before labor or after delivery, depending on the methods of recruitment. Screening may begin in the 3^rd^ trimester; however, consent and the Cannabinoid Use Survey will not be completed until after infant birth; those who consent to participate and meet eligibility criteria will all receive the INTACT intervention as there is no control group for this feasibility study. Individuals may sign consent once the infant has been born to ensure that the infant meets all inclusion/exclusion criteria. Within seven days of delivery, consent will be obtained followed by completion of the Cannabinoid Use Survey. Those meeting inclusion/exclusion criteria will receive instructions for the online sessions, and ensure they have access to complete a video phone call (having access to items such as a smart phone or laptop, etc).

Participants will be contacted via telephone within 3 weeks of giving birth to schedule the first coaching session via a cloud-based video conferencing service. Each month thereafter, the participant will complete the following two activities: 1) viewing that month’s asynchronous online module, which will provide instruction to the participant on key components of contingent parental responses; and 2) coaching session with a trained interventionist/coach who can provide tailored feedback and advice to the participant while focusing on the specific aspect of contingent parenting covered by that month’s online module. The participants will be provided access to one online module each month (12 total, including the introductory module) that they will be instructed to complete prior to the next coaching session. These INTACT intervention modules (described in the “Intervention” section) will provide instructions to the participants to support contingent caregiving. A total of 12 coaching sessions (averaging 1 per month) will occur for the participants.

The following survey will be used as stated (please see Schedule of Activities in Section 1.3):

- Cannabinoid Use Survey to be completed after consent and within 7 days of delivery

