| --- | --- | --- |
| **Endpoints:** | \| Primary Endpoints:   1. Whether a potential participant approached for study participation will eventually be consented and determined to be eligible for study participation. 2. Whether a birthing parent/infant dyad will complete the final coaching session when the child is 12 months of age. 3. Whether a birthing parent/infant dyad will complete the sufficient number of INTACT intervention coaching sessions, defined as completion of at least 8 out of 12 coaching sessions. \|  \| \| --- \| --- \| |

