## 9.3 Populations for Analyses

The population for analysis for objective 1 is that which is approached for study participation. The population for analysis for objectives 2 and 3 is consented dyads with confirmed eligibility.

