# 10 Supporting Documentation and Operational Considerations

## 10.1 Regulatory, Ethical, and Study Oversight Considerations

### 10.1.1 Informed Consent Process

To meet study objectives, we will consent up to 50 participant dyads. Birthing parent participants will then complete the Cannabinoid Use Survey for the final eligibility screen. Up to 20 eligible participant dyads will be assigned to the intervention, not including participants that withdraw from the study before beginning the first month’s coaching session. Recruitment will continue until one of these targets has been met (consent or intervention assignment).

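### Objective 1 divides by everyone approached, including women approached prenatally who have not delivered when recruitment closes and so could not have consented; the recruitment rate is biased downward by an amount that the protocol does not allow one to determine

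*Protocol*

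**What the plan says.** Protocol section 8.1 (Objective 1) takes the number approached, consented and found eligible, "divided by the number of birthing parents approached for participation". It defines the term broadly: "An approached birthing parent is defined as having a study team member discussing the trial with a possible unique participant", with two-way communication and each person counted once. The definition sets no limit on when the conversation happens. Section 9.3 repeats the choice: "The population for analysis for objective 1 is that which is approached for study participation". The endpoint in section 9.1 is "Whether a potential participant approached for study participation will eventually be consented and determined to be eligible for study participation".

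Prenatal contact is planned. Section 4.1 states "Screening may begin in the 3^rd^ trimester", and section 5.5 describes recruitment in clinics before birth as well as during the birth hospitalization. Entry to the numerator opens only later: "consent and the Cannabinoid Use Survey will not be completed until after infant birth", with both due within seven days of delivery. For women who showed interest before birth, "their due date will be noted so that study staff can monitor the hospital patient census for their delivery".

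Sections 1.1, 5.5 and 8.1 give a 3-month enrolment period. Section 10.1.1 sets ceilings of 50 consented dyads or 20 assigned to the intervention, and adds "Recruitment will continue until one of these targets has been met (consent or intervention assignment".

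**The concern.** A woman enters the denominator at her first conversation but can enter the numerator only after delivery. The third trimester is about as long as the planned enrolment period, so some women approached prenatally may still be pregnant when recruitment closes. Under the written rule each of them is a failure, although she never had the chance to consent. The text shown neither removes such women nor reports them separately, and the word for eventual consent in the endpoint has no follow-up rule behind it.

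Recruitment is a primary endpoint. Section 8.1 also says that the proportion consenting will inform how many people a larger trial must approach. If undelivered women who were still willing count as failures, refusal and ineligibility are mixed with simple lack of follow-up, and the number of approaches needed is overstated. Because the protocol itself fixes both the denominator and the analysis population, this is not a detail left to the SAP.

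**Working it through.** **Inputs.** Section 9.2 gives a null rate of 10%, a target of 20%, a one-sided exact test at 0.05, and power 0.89. It does not give the number approached. I assume N = 20 / 0.20 = 100.

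**The plan's own figure.** The rejection rule is the smallest r with P(Bin(100, 0.10) ≥ r) ≤ 0.05.
- r = 15 gives 0.073, and r = 16 gives 0.040, so r = 16.
- Power is P(Bin(100, 0.20) ≥ 16) = 0.871, against 0.89 stated.
- N = 102 gives 0.890, so the stated figure is consistent with about 100 approached.

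**Effect of undelivered women.** Let f be the share of all approached who are undelivered at closure. The protocol gives no value for f. Suppose that these women would have converted at the same true rate of 20% had they been followed to delivery. The expected observed rate is then 0.20 × (1 − f), and power is P(Bin(100, 0.20(1 − f)) ≥ 16).

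| f | Expected rate | Power at N = 100 |
|---|---|---|
| 0 | 20% | 0.871 |
| 0.05 | 19% | 0.812 |
| 0.10 | 18% | 0.737 |
| 0.20 | 16% | 0.542 |

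**If recruitment runs on to 20 eligible.** The expected number approached becomes 20 / [0.20(1 − f)], about 105, 111 and 125 for f = 0.05, 0.10 and 0.20. Twenty successes still reject 10% with up to 135 approached: P(Bin(135, 0.10) ≥ 20) = 0.048, and at 136 it is 0.052. Ignoring the 50-consent ceiling, the chance of reaching 20 within 135 approaches is P(Bin(135, p) ≥ 20). This is 0.951, 0.915, 0.860 and 0.682 for p = 0.20, 0.19, 0.18 and 0.16. Power still falls, but from a higher level and by less.

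**How f might arise (illustration only).** Assume prenatal approaches spread evenly over 13 weeks, remaining gestation uniform over 0 to 12 weeks, and closure at 13 weeks. About 46% of prenatal approaches are then undelivered. If 10%, 25% or 50% of approaches are prenatal, f is about 0.05, 0.12 or 0.23, and the expected rate is 19.1%, 17.7% or 15.4%.

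**Restricted denominator.** Counting only those whose consent window has closed returns the expected rate to 20% on a smaller n. Exact power is 0.82 at n = 90 and 0.75 at n = 80. With the same 100 approached, the all-approached rule gives 0.74 and 0.54.

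**The case against.** The decisive input is missing. Posting or handing out a flyer is not an approach, since section 8.1 requires a two-way conversation with a study team member. The main inpatient route (sections 4.1 and 5.5) finds women during the birth hospitalization, when delivery is at hand. With mostly inpatient recruitment f would be small. Three months is also a planned duration, while section 10.1.1 ties closure to the targets. If recruitment runs longer, fewer women remain undelivered at the end. All of this stands, and it limits the size of the effect.

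A reader might infer that half of prenatal approaches are lost, or that power falls to about 0.32. The documents do not support either. The first needs a hard close at 3 months and evenly spread approaches. The second needs in addition a prenatal share of about 60% (0.60 × 0.5 = 0.30, so an expected rate of 14%) and N held at 100 despite the stop at 20 eligible. A reader might also infer that the test could pass falsely. It cannot for this reason: the bias lowers the rate, so type I error is not inflated.

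Section 1.1 defines birthing parents as those who gave birth, which might be read as excluding undelivered women. But the protocol also applies the term to pregnant clinic patients, and section 8.1 defines approached through possible participants. That reading does not settle the matter. Nor can one tell whether the participant flow figure in section 5.5 separates undelivered women, because it is not shown.

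Lastly, the all-approached ratio is a legitimate operational yield. That is a reason to keep it as a secondary figure. It does not make it a sound estimate of conversion among women who could consent.

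**Conclusion.** The point holds as a question of direction. Under the written denominator, any woman undelivered at closure who was still willing lowers both the recruitment rate and the ratio passed to the future trial. Women who declined before birth, or were already ineligible, are true non-recruits and add no bias.

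The size is unknown. The figures of 19%, 18% and 16% rest on an assumed f of 5%, 10% and 20%, and on equal conversion among the undelivered. The power figures of 0.81, 0.74 and 0.54 also assume 100 approached. The loss is smaller if recruitment continues to 20 eligible, and slight if few approaches are prenatal. The test remains conservative. The change should be made because it concerns a primary endpoint and costs little, but the trial's validity does not depend on it.

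**What to change.** In sections 8.1 and 9.3, define the primary Objective 1 denominator as approached individuals whose delivery (or due date, if delivery is not known) plus the 7-day consent window falls on or before recruitment closure. Apply the rule equally to decliners and to interested women; dropping only the undecided would leave some bias. List the others as not yet at risk, and report the all-approached ratio as a secondary figure.

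Cost: the approach log needs an expected delivery date or month for everyone approached prenatally. Prenatal screens are already logged (section 5.5) and due dates are noted for interested women (section 4.1), so the new item is the date for decliners. It must stay within what the partial HIPAA waiver allows, given the confidentiality risk described in section 2.3. The denominator is somewhat smaller, and its power does not return to the planned level (0.82 at n = 90, 0.75 at n = 80). Closure can be triggered by reaching the enrolment target, so the closure date that defines the denominator should be recorded explicitly.

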## 5.5 Strategies for Recruitment and Retention

A multi-pronged approach will be used for recruitment at all 3 sites. Individuals will be recruited prepartum in the clinic setting as well as during the birth hospitalization. As it will be critical to ensure timely consenting/enrollment, recruitment and consenting metrics will be reviewed monthly. Consenting/enrollment will be competitive, with ideally, each site contributing an equal number of participants. However, as some sites will have more recruitment barriers, no one site will be allowed to contribute more than half of the total study goal number of dyads (each site cannot enroll more than 10 dyads). In order to reach the study enrollment goal over the 3-month period, we expect a monthly enrollment rate of at least 2-3 eligible dyads per site that go on to complete the first coaching session. If noted that the number consented is not reaching the monthly target number of participants, then alternative strategies will be implemented. Additionally, if there are concerns with the rate of recruitment, the DSMB will be contacted and notified of the concern, at which time the study team will provide possible solutions, and next steps will be discussed. All consenting will occur after delivery of the infant. Please see figure 3 for additional recruitment strategies based on the state cannabinoid legalization status of each study site.

Outpatient Recruitment

Within the clinic setting, flyers will be placed in outpatient obstetrical and family medicine clinics affiliated with each of the study sites for birthing parent self-referral. Additionally, providers will be notified of the study enrollment criteria and can distribute a flyer to any pregnant individual that may qualify to participate. Flyers will also be distributed to local cannabinoid dispensaries in the states where recreational use of cannabinoids is legal. If we screen an individual prenatally who is identified via self- or outpatient healthcare provider referral, the screening will be logged. This will ensure that an individual that declines study participation or does not qualify to participate will not be re-approached during the birth hospitalization. Additionally, social media will be considered as a possible recruitment strategy. Possible strategies for the use of social media will not involve potential participants uploading anything on social media sites that would indicate they may have used marijuana during pregnancy.

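### The number to approach for the larger trial and the pilot's recruitment trigger are based on consents, although the needs they serve are stated in dyads that both consent and prove eligible

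*Protocol*

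**What the plan says.** Section 8.1 of the Protocol, Objective 1, works with two different proportions. The recruitment endpoint is the number of birthing parents "approached, consented, and determined to meet study eligibility divided by the number of birthing parents approached for participation", and its target is on the same footing: "We aim to have at least 20% of approached individuals consent and be determined to be eligible". For planning the larger trial, the same paragraph turns to another numerator: "We will calculate the consented proportion to total individuals approached to inform the number of individuals that would need to be approached". The size of that trial is given one paragraph earlier: "we would need to consent and maintain eligibility in at least 360 participants in total".

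On accrual, 8.1 sets the pilot target as consent plus confirmed eligibility, "averaging at least 6.67 individuals per month over all sites", and words the benchmark of two per site per month for the larger trial in the same way. The log it describes holds participants consented, site and date. Of this log it says: "This will allow the number of individuals consented per month to be calculated".

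Section 5.5 sets the monthly expectation at 2 to 3 eligible dyads per site that also complete the first coaching session. The action rule that follows reads: "If noted that the number consented is not reaching the monthly target number of participants, then alternative strategies will be implemented".

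Consent and eligibility are separate steps. Section 4.1 places the Cannabinoid Use Survey, which confirms use, after consent. Section 5.1 expects more consents than eligible dyads. Section 7.2 lets sites replace dyads found ineligible after consent. Section 10.1.1 says "we will consent up to 50 participant dyads" and assigns up to 20 eligible dyads, with recruitment ending when either limit is reached.

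**The concern.** Section 2.1 names recruitment feasibility and an estimate of the recruitment rate among the key things the pilot must supply for the larger trial. If a requirement in eligible participants is divided by a proportion that counts consents, the number to approach comes out too small whenever anyone fails eligibility after consent. The error can only run in the optimistic direction.

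The trigger in 5.5 has the same mismatch: a count of consents is held against a target in eligible dyads, with first-session completion as a further condition. Enrollment lasts three months, so a trigger that fires late leaves little time to recover.

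**Working it through.** **Inputs.** Protocol 8.1: 360 consented and eligible for the larger trial; target recruitment proportion 20%; 6.67 per month over all sites. Sections 5.5 and 9.2: three months of enrollment, 20 eligible dyads. Section 10.1.1: limits of 50 consents and 20 assigned dyads. The number approached is not stated. I assume 20 / 0.20 = 100, the number at which 20 eligible dyads meet the 20% target exactly. The share of consented dyads that prove eligible is not stated either, so a range is shown.

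**The plan's own figure.** 20 eligible dyads / 3 months = 6.67 per month. This reproduces 8.1 and confirms that 6.67 is a rate of eligible dyads, not of consents.

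**Number to approach.** Let A be approached, C consented and E consented and eligible.

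- Needed: 360 / (E/A) = 360 / 0.20 = 1,800.
- By the 8.1 sentence: 360 / (C/A).
- Ratio of the two: (360·A/E) / (360·A/C) = C/E. It does not depend on the assumed A.

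| Consents per 20 eligible | C/A | Approaches by 8.1 | Needed | Understated by | Eligible obtained at 20% |
|---|---|---|---|---|---|
| 20 | 0.20 | 1,800 | 1,800 | 1.0-fold | 360 |
| 25 | 0.25 | 1,440 | 1,800 | 1.25-fold | 288 |
| 30 | 0.30 | 1,200 | 1,800 | 1.5-fold | 240 |
| 40 | 0.40 | 900 | 1,800 | 2.0-fold | 180 |
| 50 | 0.50 | 720 | 1,800 | 2.5-fold | 144 |

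**Trigger.** Suppose consents run at exactly 6.67 per month, so that the 5.5 rule sees the target as met. Eligible dyads per month = 6.67 × E/C; over three months, 20 × E/C.

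| E/C | Eligible per month | Eligible in 3 months (goal 20) |
|---|---|---|
| 20/25 = 80% | 5.33 | 16 |
| 20/30 = 67% | 4.44 | 13.3 |
| 20/40 = 50% | 3.33 | 10 |
| 20/50 = 40% | 2.67 | 8 |

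In none of these rows would the rule as written call for alternative strategies. Losses between eligibility and the first coaching session would widen the gap to the 5.5 target further.

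**Is there a largest value?** With both limits reached together, C/E = 50/20 = 2.5. If recruitment ends at 50 consents with fewer than 20 eligible, the ratio is higher: 50/15 = 3.3, 50/10 = 5. If the 20-dyad limit is reached first, it is 2.5 or less and may be near 1. Eligible dyads that withdraw before the first session do not count toward the 20, so there could also be more than 20 eligible among 50 consents; 25 would give 50/25 = 2.0.

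**The case against.** The strongest reply is that the right figure will be available. The consented-and-eligible proportion is the Objective 1 endpoint and is tested in 9.4.2. Section 8.1 tracks approached, consented and eligible, and it says only that the consented proportion will inform planning, not that it is the sole input. This limits the harm: no pilot test, threshold or conclusion changes. It does not remove an explicit statement that names the wrong numerator for the purpose, a few lines after the right one was defined.

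A second reply is that 5.5 also provides for monthly review of recruitment and consenting metrics and for telling the DSMB about concerns over the recruitment rate. That is a real safeguard, but no count is attached to it, so it does not repair the one rule that names a count. Nor can the word for consent in 5.5 safely be taken as shorthand for eligible, because 5.1 and 10.1.1 keep the two apart.

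Two stronger readings are tempting and should be resisted. A reader might infer that accrual planning for the larger trial rests on consents. It does not: 8.1 words both the pilot target and the benchmark of two per site per month as consent with confirmed eligibility, and only the log and the monthly count taken from it fall short. A reader might also take 2.5-fold as the maximum or likely error, from the limits of 50 and 20. It is only the ratio of two recruitment limits. Sections 4.1 and 10.1.1.2 screen for eligibility before consent, which may keep the ratio near 1, while reaching 50 consents with fewer than 20 eligible would take it above 2.5.

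**Conclusion.** The point holds for two rules: the planning proportion in 8.1 and the trigger in 5.5. Both count consents where the quantity they serve counts dyads that consent and prove eligible, and the protocol itself expects the two to differ. The number to approach is understated by the ratio of consented to eligible, whatever that proves to be. Over an illustrative range of 25 to 50 consents per 20 eligible, the figure would be 1,440 down to 720 instead of 1,800, and the trigger could stay silent while 16 down to 8 of the 20 dyads accrue in three months. These figures assume 100 approached, the 20% target exactly met, and constant monthly consents and eligibility share. They are not predictions, since the protocol gives no rate of eligibility failure after consent. The correction should be made, but it concerns planning and monitoring, not the validity of the pilot's own analysis.

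**What to change.** - **Section 8.1, planning sentence:** derive the number to approach from those consented and confirmed eligible, divided by those approached. Keep the consent proportion as a descriptive figure, since it shows where in the process people are lost.
- **Section 8.1, log:** also record the date on which eligibility is confirmed, so that eligible dyads per site and month can be counted against the target and benchmark already stated there.
- **Section 5.5, trigger:** compare dyads consented and confirmed eligible with the monthly target. Reconcile this with the target's condition that dyads complete the first coaching session, which the 8.1 target does not carry. Either use one definition in both sections, or monitor first-session completion as a separate count.

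The cost is a few sentences and one date field, since the counts are already tracked. The planning figure may be less favorable and the trigger may fire earlier.
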